**Table 7a. Summary of screening Status and severity of anxiety and depression**

| Screened by | Visit             | ---Screening Status--- |                    |                    | -----Anxiety----- |                   |               | -----Depression----- |                   |               |
|-------------|-------------------|------------------------|--------------------|--------------------|-------------------|-------------------|---------------|----------------------|-------------------|---------------|
|             |                   | N                      | Positives
n (%) | Negatives
n (%) | Mild
5-9       | Moderate
10-14 | Severe
≥15 | Mild
5-9          | Moderate
10-14 | Severe
≥15 |
| ASHA        | Baseline          | xxxxx                  | xxxx (xx.xx)       | xxxx (xx.xx)       | xxx (xx.xx)       | xxx (xx.xx)       | xxx (xx.xx)   | xxx (xx.xx)          | xxx (xx.xx)       | xxx (xx.xx)   |
|             | Post Intervention | xxxxx                  | xxxx (xx.xx)       | xxxx (xx.xx)       | xxx (xx.xx)       | xxx (xx.xx)       | xxx (xx.xx)   | xxx (xx.xx)          | xxx (xx.xx)       | xxx (xx.xx)   |
| Interviewer | Baseline          | xxxxx                  | xxxx (xx.xx)       | xxxx (xx.xx)       | xxx (xx.xx)       | xxx (xx.xx)       | xxx (xx.xx)   | xxx (xx.xx)          | xxx (xx.xx)       | xxx (xx.xx)   |
|             | Post Intervention | xxxxx                  | xxxx (xx.xx)       | xxxx (xx.xx)       | xxx (xx.xx)       | xxx (xx.xx)       | xxx (xx.xx)   | xxx (xx.xx)          | xxx (xx.xx)       | xxx (xx.xx)   |

**Table 7b: Summary of Anxiety and Depression Score of ASHA screen positive**

| Category   | Severity | Total Score | Baseline
(N=xx)
n (%) | Post intervention
(N=XX)
n (%) |
|------------|----------|-------------|-----------------------------|--------------------------------------|
| Anxiety    | Normal   | 0-4         | xxxx(xx.xx)                 | xxxx(xx.xx)                          |
|            | Mild     | 5-9         | xxxx(xx.xx)                 | xxxx(xx.xx)                          |
|            | Moderate | 10-14       | xxxx(xx.xx)                 | xxxx(xx.xx)                          |
|            | Severe   | ≥15         | xxxx(xx.xx)                 | xxxx(xx.xx)                          |
| Depression | Normal   | 0-4         | xxxx(xx.xx)                 | xxxx(xx.xx)                          |
|            | Mild     | 5-9         | xxxx(xx.xx)                 | xxxx(xx.xx)                          |
|            | Moderate | 10-14       | xxxx(xx.xx)                 | xxxx(xx.xx)                          |
|            | Severe   | ≥15         | xxxx(xx.xx)                 | xxxx(xx.xx)                          |

*N=Total no of patients in particular visit. n=No. of patients in particular category Patient is counted only once in either category.*

**Table 7c: Summary of Patients who are Screened positive by ASHAs.**

|                                  | Baseline(N=xxxxx) | Post Intervention(N=xxxxx) |
|----------------------------------|--------------------------|-----------------------------------|
|                                  | N(%)              | N(%)                       |
| Depression Score >=10            | xxx (xx.xx)              | xxx (xx.xx)                       |
| Anxiety Score >=10               | xxx (xx.xx)              | xxx (xx.xx)                       |
| Suicide risk Score >=1           | xxx (xx.xx)              | xxx (xx.xx)                       |
| Anxiety or Depression Score >=10 | xxx (xx.xx)              | xxx (xx.xx)                       |

*N=Total no. of patients who are screened positives. Percentages are calculated based on patients who were screened positive.*

Table 8a: Change in Depression/Anxiety Score from Baseline to Post Intervention in screen positive

| Screened by | Visit             | -----Anxiety----- |               |        |            |         | -----Depression----- |               |        |            |         |
|-------------|-------------------|-------------------|---------------|--------|------------|---------|----------------------|---------------|--------|------------|---------|
|             |                   | N                 | Mean (SD)     | Midian | Min, Max   | P-value | N                    | Mean (SD)     | Midian | Min, Max   | P-value |
| ASHA        | Baseline          | xxxxx             | xx.xx (x.xxx) | xx.xx  | xx.x, xx.x |         | xxxxx                | xx.xx (x.xxx) | xx.xx  | xx.x, xx.x |         |
|             | Post Intervention | xxxxx             | xx.xx (x.xxx) | xx.xx  | xx.x, xx.x |         | xxxxx                | xx.xx (x.xxx) | xx.xx  | xx.x, xx.x |         |
|             | Difference        | xxxxx             | xx.xx (x.xxx) | xx.xx  | xx.x, xx.x | 0.xxx   | xxxxx                | xx.xx (x.xxx) | xx.xx  | xx.x, xx.x | 0.xxx   |
| Interviewer | Baseline          | xxxxx             | xx.xx (x.xxx) | xx.xx  | xx.x, xx.x |         | xxxxx                | xx.xx (x.xxx) | xx.xx  | xx.x, xx.x |         |
|             | Post Intervention | xxxxx             | xx.xx (x.xxx) | xx.xx  | xx.x, xx.x |         | xxxxx                | xx.xx (x.xxx) | xx.xx  | xx.x, xx.x |         |
|             | Difference        | xxxxx             | xx.xx (x.xxx) | xx.xx  | xx.x, xx.x | 0.xxx   | xxxxx                | xx.xx (x.xxx) | xx.xx  | xx.x, xx.x | 0.xxx   |

Table 8b: Change in Depression/Anxiety Score from Baseline to Post Intervention for those who had a score  $\geq 10$  at the beginning of the intervention as screened by ASHAs

| Visit             | -----Anxiety----- |               |        |            |         | -----Depression----- |               |        |            |         |
|-------------------|-------------------|---------------|--------|------------|---------|----------------------|---------------|--------|------------|---------|
|                   | N                 | Mean (SD)     | Midian | Min, Max   | P-value | N                    | Mean (SD)     | Midian | Min, Max   | P-value |
| Baseline          | xxxxx             | xx.xx (x.xxx) | xx.xx  | xx.x, xx.x |         | xxxxx                | xx.xx (x.xxx) | xx.xx  | xx.x, xx.x |         |
| Post Intervention | xxxxx             | xx.xx (x.xxx) | xx.xx  | xx.x, xx.x |         | xxxxx                | xx.xx (x.xxx) | xx.xx  | xx.x, xx.x |         |
| Difference        | xxxxx             | xx.xx (x.xxx) | xx.xx  | xx.x, xx.x | 0.xxxx  | xxxxx                | xx.xx (x.xxx) | xx.xx  | xx.x, xx.x | 0.xxxx  |

**Table 9a: Summary of stressful question for the Patients who are Screened Positive by ASHA**

| Questions                                                                                                                                        | N=(xx) n(%) |
|---------------------------------------------------------------------------------------------------------------------------------------------------------|--------------------|
| Did you get married in the last 1 year?                                                                                                                 | xxx (xx.xx)        |
| Did you get separated/divorced in the last 1 year?                                                                                                      | xxx (xx.xx)        |
| Did your spouse die in the last 1 year?                                                                                                                 | xxx (xx.xx)        |
| Did any of your loved ones die in the last 1 year?                                                                                                      | xxx (xx.xx)        |
| Did you have a baby in the last 1 year?                                                                                                                 | xxx (xx.xx)        |
| Did you lose your job in the last 1 year?                                                                                                               | xxx (xx.xx)        |
| Did you retire in the last 1 year?                                                                                                                      | xxx (xx.xx)        |
| Did you or your loved one suffer any major illness/injury in the last 1 year?                                                                           | xxx (xx.xx)        |
| Did you have any problems with your boyfriend/girlfriend in the last 1 year?                                                                            | xxx (xx.xx)        |
| Did you have any major problems with your school/college performance in the last 1 year?                                                                | xxx (xx.xx)        |
| Did you have any major financial problems in the last year?                                                                                             | xxx (xx.xx)        |
| Did you face any natural disaster or stolen livestock or death of livestock, or crop failure or forced migration leading to loss of income or property? | xxx (xx.xx)        |
| Did you experience any major crime or were a victim of a major crime like robbery, assault/beating, murder/attempted murder, sexual violence?           | xxx (xx.xx)        |

*N=Total no. of screen positive patients. n=No. of patients in particular category*

**Table 9b: Summary of stressful events among the Patients who have Depression or Anxiety Score  $\geq 10$**

*The shell of table 10b will be exact similar to Table 10a.*

**Table 10: Summary of Stressful Events for the Patients who are Screened Positive by ASHA**

| Number of Stressful events                                            | (N=xxxx)
n(%) |
|-----------------------------------------------------------------------|------------------|
| 0                                                                     | xxx (xx.xx)      |
| 1                                                                     | xxx (xx.xx)      |
| 2-3                                                                   | xxx (xx.xx)      |
| >=4                                                                   | xxx (xx.xx)      |
| Descriptive Statistics (Patients who have total score greater than 1) |                  |
| N                                                                     | xxxx             |
| Mean (SD)                                                             | x.xx (x.xxx)     |
| Median                                                                | x.xx             |
| Min, Max                                                              | x, x             |

*N=Total no. of patients in Baseline; n=No. of patients in particular category*

**Table 11: Summary of Sharing Personal Problems for the Patients who are Screened Positive by ASHA**

|                                                               | (N=xxxx)
n(%) |
|---------------------------------------------------------------|------------------|
| When you have a personal problem do you share it with anyone? | xx(xx.xx%)       |

*N=Total no. of patients in Baseline; n=No. of patients in particular category*

Table 12: Summary of Assessment of Alcohol and Substance Use for the ASHA screened positive Patients

| Question                                                   | Baseline (N=xxxxx)
n (%) | Post Intervention (N=xxxxx)
n (%) |
|------------------------------------------------------------|-----------------------------|--------------------------------------|
| Tobacco products (cigarettes, bidi, gutka, cigars, etc.)   | xxx (xx.xx)                 | xxx (xx.xx)                          |
| Alcoholic beverages (beer, wine, spirits, etc.)            | xxx (xx.xx)                 | xxx (xx.xx)                          |
| Cannabis (marijuana, pot, grass, hash, etc.)               | xxx (xx.xx)                 | xxx (xx.xx)                          |
| Cocaine (coke, crack, etc.)                                | xxx (xx.xx)                 | xxx (xx.xx)                          |
| Opioids (heroin, morphine, methadone, codeine, etc.)       | xxx (xx.xx)                 | xxx (xx.xx)                          |
| Amphetamine type stimulants (speed, diet pills, ecstasy,   | xxx (xx.xx)                 | xxx (xx.xx)                          |
| Inhalants (nitrous, glue, petrol, paint thinner, etc.)     | xxx (xx.xx)                 | xxx (xx.xx)                          |
| Sedatives or Sleeping Pills (Valium, Serepax, Rohypnol,    | xxx (xx.xx)                 | xxx (xx.xx)                          |
| Hallucinogens (LSD, acid, mushrooms, PCP, Special K, etc.) | xxx (xx.xx)                 | xxx (xx.xx)                          |
| Other - specify:                                           | xxx (xx.xx)                 | xxx (xx.xx)                          |

*N=Total no. of patients in Baseline; n=No. of patients in particular category*

Table 13: Summary of Past History of the ASHA screened positive Patients

| Question                                                                           | Baseline (N=xxxxx)
n (%) |
|------------------------------------------------------------------------------------|-----------------------------|
| Have you ever been told by a health provider that you have heart attack or angina? | (xx.xx) xxx                 |
| Have you ever been told by a doctor that you have or had Stroke?                   | (xx.xx) xxx                 |
| Have you ever been told by a doctor that you have or have had Diabetes?            | (xx.xx) xxx                 |
| Have you ever been told by a doctor that you have or have had Cancer?              | (xx.xx) xxx                 |
| Have you ever been diagnosed to have any mental disorder?                          | (xx.xx) xxx                 |
| Did you get treated for that mental disorder?                                      | (xx.xx) xxx                 |

*N=Total no. of patients in Baseline; n=No. of patients in particular category*

*Percentages for (Did you get treated for that mental disorder? ) Is calculated on number of patients diagnosed for mental disorder.*

Table 14a: Summary of treatment History among ASHA screened positive Patients

| Question                                                               | Baseline(N=xxxx)
n(%) |
|------------------------------------------------------------------------|--------------------------|
| Are you currently taking any western medicines regularly?              | xx(xx.xx)                |
| Are you currently taking any medicines for mental disorders regularly? | xx(xx.xx)                |

*N=Total no. of patients in Baseline; n=No. of patients in particular category*

Table 14b: Summary of treatment History during intervention among ASHA screened positive Patients

| Question                                                                              | Baseline(N=xxxx)
n(%) |
|---------------------------------------------------------------------------------------|--------------------------|
| Did you get treated for your mental health condition as indicated by ASHA/Interviewer | xx(xx.xx)                |

*N=Total no. of patients in Baseline; n=No. of patients in particular category*

Table 14c: Summary of treatment compliance among treated patients of ASHA screened positive

| Question                                                                            | Baseline(N=xxxx)
n(%) |
|-------------------------------------------------------------------------------------|--------------------------|
| Did you take medicines as prescribed by the primary care doctor on a regular basis? | xx(xx.xx)                |

*N=Total no. of patients in Baseline; n=No. of patients in particular category*

Table 15: Summary of for Utilization of Health Services for Screen Positive subjects

| Screen Positive | Health Service used ** | Baseline
(N=xxxxx)
n (%) | Post Intervention
(N=xxxxx)
n (%) | P-value |
|-----------------|------------------------|--------------------------------|-----------------------------------------|---------|
| By ASHA         | Yes                    | xxx (xx.xx)                    | xxx (xx.xx)                             | 0.xxxx  |
|                 | No                     | xxx (xx.xx)                    | xxx (xx.xx)                             |         |
| By Interviewer* | No                     | xxx (xx.xx)                    | xxx (xx.xx)                             | 0.xxxx  |
|                 | Yes                    | xxx (xx.xx)                    | xxx (xx.xx)                             |         |

\* This includes only those patients who were screen positive by Study Interviewer but not by ASHA.

\*\* Health Service used: At baseline: Response from the question "Did you get treated for that mental disorder?"

At Post Intervention: Response from the question "Did you get treated for your mental health condition as indicated by ASHA/Interviewer?"

P-Value is calculated based on Mc-nimar test for matched pair test of proportion.

Table 16a: Case control analysis of Change in Depression/Anxiety Score from Baseline to Post Intervention for those who had a score  $\geq 10$  at the beginning of the intervention.

| Category   | Type    | Statistics | Baseline     | Post Intervention | Change       | P-Value for difference |
|------------|---------|------------|--------------|-------------------|--------------|------------------------|
| Anxiety    | Cases   | N          | xxxxx        | xxxxx             | xxxxx        | 0.xxxx                 |
|            |         | Mean (SD)  | xx.x (xx.xx) | xx.x (xx.xx)      | xx.x (xx.xx) |                        |
|            |         | Median     | xx.x         | xx.x              | xx.x         |                        |
|            |         | Min, Max   | xx; xx       | xx; xx            | xx; xx       |                        |
|            | Control | N          | xxxxx        | xxxxx             | xxxxx        |                        |
|            |         | Mean (SD)  | xx.x (xx.xx) | xx.x (xx.xx)      | xx.x (xx.xx) |                        |
|            |         | Median     | xx.x         | xx.x              | xx.x         |                        |
|            |         | Min, Max   | xx; xx       | xx; xx            | xx; xx       |                        |
| Depression | Cases   | N          | xxxxx        | xxxxx             | xxxxx        | 0.xxxx                 |
|            |         | Mean (SD)  | xx.x (xx.xx) | xx.x (xx.xx)      | xx.x (xx.xx) |                        |
|            |         | Median     | xx.x         | xx.x              | xx.x         |                        |
|            |         | Min, Max   | xx; xx       | xx; xx            | xx; xx       |                        |
|            | Control | N          | xxxxx        | xxxxx             | xxxxx        |                        |
|            |         | Mean (SD)  | xx.x (xx.xx) | xx.x (xx.xx)      | xx.x (xx.xx) |                        |
|            |         | Median     | xx.x         | xx.x              | xx.x         |                        |
|            |         | Min, Max   | xx; xx       | xx; xx            | xx; xx       |                        |

\* Case: The subjects who are screen positive by ASHA.

\*\* Control: The subjects who are screened negative by ASHA but positive by study interviewer.

P-Value is calculated based chi-square independent sample test of proportion.

Table 16b: Case control analysis for health service utilization

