**Smart mental health Visit schedule and analysis for visit:**

The study will be reported in mainly 2 category:-

1. Baseline (As applicable, this will includes ASHA screening data available in in ASHA Screening 1 and ASHA follow up 1. OR Baseline data collected by study interviewers)
2. Post Intervention (collected by study interviewers)

All the subject at post intervention are screen positive subjects. They were screened positive either at Baseline by study interviewers or at Intervention visits (ASHA screening 1 and ASHA follow-up 1) by ASHA. All the screen positive subjects were followed by ASHAs which is available in the ASHA follow up data.

Unless otherwise stated, the summary tables will be presented under 2 category:-

1. Baseline
2. Post Intervention

The difference between Baseline and Post Intervention will provide effect of intervention.

Apart from the Post Intervention data, post stigma data was also collected. At the time of creating derived data for post Intervention, both data (Post Intervention and post stigma) are appended together and created a single data set. A flag variable containing record ("Post Intervention" & "post stigma") was created was created in derived data set to identify such records.

Unless otherwise stated, all the analysis will be presented for all the subject who are screen positive by ASHA.

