**Smart mental health Final Statistical Analysis plan Primary Analysis:**

The primary objective of the study is:-

To see the difference in anxiety and depression score and health service utilization among the mental health screen positive subject post intervention.

The screen positive subjects at baseline will be looked for their past history for mental health service utilization. The subjects who responded "Yes" against question number 56 "Did you get treated for that mental disorder?" are proportion of subject at baseline who used mental health service.

At post intervention, the number of subjects used health service can be taken from Doctors follow-up data.

The count and percentage will be provided for the subjects who are screen positive for utilization of health services. Proportion of mental health service utilization at baseline and post intervention among the screen positive subject will be statistically analyze by McNemar test. The P-value for comparison of will be presented in same table.

A separate table will be provided for subjects screen positive subjects who actually visited doctor for their treatment at time of intervention. The count and percent by visit will be provided for this.

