#### **Case control Analysis of Primary objective:**

All the subjects screened positive by ASHA are case here. The subjects who mental health are screen negative by ASHA, but screen positive by interviewer are kind of control in this study setup. Such subjects will be called as control.

A case control analysis will be performed to assess the difference in anxiety and depression score and mental health service utilization.

For this difference in anxiety and depression score for individual subjects will be computed from ASHA screen data and post intervention data. Further this difference in case and control will be statistically analyses by 2 independent sample t-test. Difference of difference in score between case and control along with p-value will be presented.

For health service utilization between cases and control, Count along with percent and Chi- square P-value will be presented.

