#### **Secondary Analysis Depression and Anxiety Score:**

The subjects are classified as screen positive if he/she fulfil either one of below mentioned three category:-

1. Depression Sore  $\geq 10$
2. Anxiety Score  $\geq 10$
3. Suicidal tendency Score  $\geq 1$

The depression and anxiety will be categorized as Normal if their total score is in between 0-

4. The score in between 5-9 will be classify as Mild. The score in between 10-14 will be classify as moderated. The score of 15 or greater will be treated as severe.

The Anxiety and Depression score will be categorized by their severity. The count and percentage for depression and Anxiety at baseline and post baseline will be presented by severity. A separate table will be presented for depression score  $\geq 10$  and anxiety score  $\geq 10$  at baseline and post intervention.

A separated table will be provides for the only screen positive subjects with the count and percentage of the symptoms which lead them to be screen positive.

The summary statistics (N, Mean, STD, Min and Max) for anxiety and depression score by visit will be presented. The difference in score between baseline and post intervention will be summarized in similar fashion. The mean difference in score between baseline and post intervention will be statistically analyzed by paired t-test. The p-value from the analysis will be presented in same table.

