**Proportion of subject used health services**

| Category | Baseline | Post Intervention | P-Value |
|-----------------|-----------------|--------------------------|----------------|
| Case*           | xxxx            | xxxx                     | 0.xxx          |
| Control**       | xxxx            | xxxx                     |                |

*Health Service used: At baseline: Response from the question “Did you get treated for that mental disorder?”*

*At Post Intervention: Response from the question “Did you get treated for your mental health condition as indicated by ASHA/Interviewer?”*

*\* Case: The subjects who are screen positive by ASHA.*

*\*\* Control: The subjects who are screened negative by ASHA but positive by study interviewer.*

*P-Value is calculated based chi-square independent sample test of proportion.*

Table 17: Subject Referrals during ASHA screening

| Screened by |                                                                                                            | (N*=xxxxxx)
n(%) |
|-------------|------------------------------------------------------------------------------------------------------------|---------------------|
| ASHA        | Out of those Screened by ASHA Proportion of subject referred to the PHC doctor                             | xxxx (xx.xx)        |
|             | Out of those referred to PHC doctors Proportion of subjects actually visited doctors                       | xxxx (xx.xx)        |
|             | Out of those visited doctors Proportion of subjects appropriately prescribed anti-depressant or anxiolytic | xxxx (xx.xx)        |
|             | Out of those visited doctors Proportion of subjects appropriately referred by the PHC doctor for more      | xxxx (xx.xx)        |

\*N= overall population screened by ASHAs.

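### Medication for a mental disorder already in use at baseline is tabulated only for ASHA screen positives and enters no comparison, so it may confound the non-randomised case-control analyses in Tables 16a and 16b

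*SAP*

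**What the plan says.** The primary objective has two parts, scores and service use: "To see the difference in anxiety and depression score and health service utilization among the mental health screen positive subject post intervention". The visit-schedule section attributes the before-after change to the programme: "The difference between Baseline and Post Intervention will provide effect of intervention".

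- **Baseline medication.** Table 14a asks "Are you currently taking any medicines for mental disorders regularly". It has one baseline column, covers ASHA screen positives only, and has no p-value. No other table or test uses the item.
- **Score change.** Within subjects: "The mean difference in score between baseline and post intervention will be statistically analyzed by paired t-test". Between cases and controls, the case-control section plans an unadjusted two-sample t-test on the individual changes. (The note under Table 16a names a chi-square test. I take the t-test in the text as intended.)
- **Groups.** Cases are positive on ASHA screening. Controls are negative on ASHA screening but positive at interview. Allocation is not random.
- **Service use between groups.** "For health service utilization between cases and control, Count along with percent and Chi- square P-value will be presented". Table 16b has a baseline column, a post-intervention column and a single p-value.
- **Baseline service use.** This is Yes to question 56, on treatment for a diagnosed disorder, and the look-back is open-ended: "The screen positive subjects at baseline will be looked for their past history for mental health service utilization".
- **Post-intervention service use.** Tables 15 and 16b use the interview question "Did you get treated for your mental health condition as indicated by ASHA/Interviewer". The Primary Analysis text instead points to the doctors' follow-up records.
- **Service use within subjects.** Table 15 uses McNemar's test.

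**The concern.** Cases and controls are formed by how two screening sources disagree, so nothing makes them alike in treatment already under way. The one item that measures current treatment is shown for cases only, and a reader cannot check the balance.

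Two results are exposed. In Table 16a, earlier treatment that is still changing scores contributes to the difference between groups. In Table 16b, the post-intervention question asks whether the person was treated, not whether treatment was new. A patient who simply continues can answer Yes. If the groups differ in how many such patients they hold, the post-intervention proportions differ even when newly started care is equal. Both results bear on the primary objective.

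**Working it through.** The SAP gives no sample size, rate, standard deviation or share on medication, so there is no stated figure to reproduce. All numbers below are assumptions that show how each planned test behaves.

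**1. Table 15 (McNemar).** The tested difference is (b − c)/N, where b counts No-to-Yes pairs and c counts Yes-to-No pairs. Assume N = 500, b = 100, c = 10 and k continuing patients.

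- If the k patients are Yes on question 56 and Yes afterwards, they are concordant: (100 − 10)/500 = 18.0 points for any k. Only the raw post-intervention proportion, (100 + k)/500, moves: 20%, 21%, 25%, 30% and 40% for k = 0, 5, 25, 50 and 100.
- If they are on medication but are entered as No on question 56, they join b: (100 + k − 10)/500 = 19, 23, 28 and 38 points for k = 5, 25, 50 and 100. With no true change, k = 25 gives 25/500 = 5 points, exact p = 2 × 0.5^25 = 6e-8.

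The second case needs patients who take such medicines but are not Yes on question 56. It can arise because Table 13 bases the question 56 percentage on patients with a reported diagnosis, so others may be missing and then set to No. The SAP does not say how they are handled.

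**2. Table 16b (unpaired chi-square), if the post-intervention column is tested.** Proportion of users = q + (1 − q) × r, where q is the share continuing and r is new use. Assume r = 20% in both groups and q = 2% in controls, so controls show 0.02 + 0.98 × 0.20 = 21.6%.

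| q in cases | Cases | Spurious difference | p, 400 v 100 | p, 400 v 400 |
|---|---|---|---|---|
| 2% | 21.6% | 0.0 points | 1.0 | 1.0 |
| 5% | 0.05 + 0.95 × 0.20 = 24.0% | 2.4 points | 0.61 | 0.42 |
| 10% | 0.10 + 0.90 × 0.20 = 28.0% | 6.4 points | 0.20 | 0.04 |
| 15% | 0.15 + 0.85 × 0.20 = 32.0% | 10.4 points | 0.04 | 0.001 |

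The difference in newly started care is zero in every row. If controls held the larger share, the sign would reverse. If the baseline column is tested, the p-value says nothing about the intervention.

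**3. Score change.** Let d be the mean change in already-treated subjects that comes from the earlier treatment. Bias in the within-group mean change is q × d:

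- d = 0 (stable treatment): 0
- q = 5%, d = 1 to 5: 0.05 to 0.25 points
- q = 20%, d = 1 to 5: 0.2 to 1.0 points

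For cases against controls with the same d, the bias is (q in cases − q in controls) × d. For example, (0.10 − 0.02) × 3 = 0.24 points. It vanishes if the shares are equal or d is 0.

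**The case against.** A reader might infer that the plan credits continuing treatment to the intervention throughout, including the main service-use test. The documents do not support that. Earlier treatment is the baseline measure in Table 15: the Yes answers to question 56 "are proportion of subject at baseline who used mental health service". Continuing patients coded Yes twice drop out of McNemar's test. Because question 56 has no time window, it more likely overstates baseline use and so understates the gain. This part of the objection stands.

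It also stands that treatment already in place acts on the baseline score as well. Continuation biases the change only if its effect is still moving, and long-treated patients who remain symptomatic could dilute the change instead.

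A reader might also suppose that ASHAs flag people they know to be under treatment, which would concentrate treatment among cases. The SAP sets screen positivity by depression, anxiety and suicidal-tendency scores alone, so that mechanism is conjecture.

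It can further be said that Table 16b prints baseline service use beside the post-intervention figure, and that the post-intervention question, or the doctors' records, may not capture continued care. The first point helps only in part: question 56 mixes past with current treatment and does not replace the medication item, and an unpaired test on one column does not use the other. The second is unresolved, because the SAP names two sources and defines neither with respect to continued care.

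Finally, adjusting for one covariate does not make two non-randomised groups equivalent. That is true, but it does not justify leaving out a relevant baseline item already collected.

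**Conclusion.** The point holds for the case-control analyses. Current medication at baseline is collected, shown for cases only and used in no comparison. It may confound the difference in score change in Table 16a. It may confound service use in Table 16b if the post-intervention column is tested, which the SAP does not state. Table 15 is exposed only through patients on medication who are not Yes on question 56. The unadjusted within-group score changes in Tables 8a and 8b may also carry some effect of earlier treatment, but only where that effect is still developing.

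Neither the size nor the direction can be derived from the document. The illustrative 2.4 to 10.4 points for Table 16b, and 0 to 1.0 score points within a group, rest on assumed shares and effects. They also assume, for Table 16b, that every continuing patient is counted as a user. The plan should be amended, but nothing here shows that its results would be wrong.

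**What to change.** 1. Show Table 14a by case and control, taking the controls' answers from the interviewer baseline data. First confirm that the item was asked there.
2. Adjust the case-control comparison of score change (Table 16a) for baseline treatment, yes or no, and report it beside the planned unadjusted result.
3. State that the chi-square in Table 16b tests the post-intervention column. Also present the table restricted to subjects not on treatment at baseline, or stratified by that status.
4. Report Tables 8a and 8b with and without subjects on treatment at baseline, as a sensitivity analysis.
5. Keep the planned Table 15 analysis.

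The cost is a few sentences in the SAP and extra versions of existing tables from an item already collected. The downside is slightly fewer subjects, and so less precision, in the restricted versions. Other differences between cases and controls remain, and the text should say so.
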